### Aims

There are three aims of this trial. The first is to assess the efficacy of a behaviour change intervention (Healthy Conversation Skills) in improving the diet quality of pregnant women. The second is to assess the efficacy of oral daily vitamin D supplementation in improving the vitamin D status of pregnant women. The third is to explore the efficacy of an intervention combining vitamin D supplementation and behaviour change support in improving the diet quality and nutritional status of pregnant women.

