### Randomisation

Consistent with the trial’s factorial design, women are randomised to receive Healthy Conversation Skills support or to usual care and to receive a vitamin D supplement or a matched placebo. The impartial trial data manager uses block randomisation to allocate participants to receive support from a practitioner trained in Healthy Conversation Skills, or to usual care. Blocks of 4 are used, each with two 0’s and two 1’s. This ensures that for each 4 participants randomised there will be equal distribution of intervention and control participants. While is it not possible to blind staff to the allocation ﻿of Healthy Conversation Skills, the women themselves will not be told what the intervention entails and so will be blind to the intervention they are receiving. The IMP is pre-randomised by the manufacturer using a computer system. The women are blind to their vitamin D allocation, as are the research team.

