### Sample size and power calculation

Our power calculation uses an alpha of 0.025 taking into account the two primary outcomes of maternal vitamin D and maternal diet quality. With 150 participants in each arm of the trial (equivalent to 300 participants per arm in each comparison between HCS and routine care and between vitamin D and placebo) there is 80 % power at an alpha of 0.025 to detect a 0.25 standard deviation difference in both diet quality score and vitamin D (approximately 3 nmol/l 25(OH)) between groups. Allowing for a 20 % drop-out rate, we aim to recruit 188 women to each arm of the four arms of the trial in order to achieve 150 women in each arm. Pilot data suggest that around 40 % of women who are approached will agree to participate in the study, and so initial invitations will be issued to 1250 women. Experience in the MAVIDOS trial indicates that women will be recruited at a rate of 5–8 per week, suggesting that recruitment will take up to 3 years.

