### Statistical analyses

We will perform a complete case analysis for each outcome using *t* tests to compare the two primary outcomes between the relevant intervention arms. Multiple linear regression will be used to adjust for any differences identified at baseline. Similar analyses will be conducted for the secondary outcomes. The neonatal bone and body composition analyses will include stratification by season of birth in light of recent findings from the MAVIDOS trial [10]. We will also conduct exploratory analyses of the interaction between HCS and vitamin D on both primary outcomes. For binary outcomes, chi-squared tests or Fisher’s exact test for rare outcomes will be used. To adjust for imbalances at baseline, logistic regression will be used, or for rare outcomes, binary regression or Poisson regression with robust variance.

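### The main-effect t tests of this 2x2 factorial leave out the other randomised factor; they are valid but less precise than a model with both factors, which would cost almost nothing

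*Protocol article*

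**What the plan says.** Under Study design, the article describes a two-by-two factorial of HCS support against usual care and vitamin D against placebo. Statistical analyses then names the method: t "tests to compare the two primary outcomes between the relevant intervention arms". Multiple linear regression is mentioned only for differences found at baseline. Secondary outcomes get similar analyses, with chi-squared or exact tests for binary outcomes and regression there for baseline imbalance. Both randomised factors appear together only in an exploratory interaction analysis.

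Sample size and power calculation gives 150 women per cell, "equivalent to 300 participants per arm in each comparison between HCS and routine care and between vitamin D and placebo", with 80% power at alpha 0.025 for a "0.25 standard deviation difference in both diet quality score and vitamin D", about 3 nmol/l for the latter.

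Under Aims, HCS is paired with diet quality and vitamin D with vitamin D status. The third aim is to "explore the efficacy of an intervention combining vitamin D supplementation and behaviour change support in improving the diet quality and nutritional status".

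Under Randomisation, the data manager allocates HCS in blocks of 4, while for the capsules "The IMP is pre-randomised by the manufacturer using a computer system". The article describes no joint balancing of the two allocations.

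**The concern.** In a factorial trial, each side of a comparison on one factor mixes women who did and did not receive the other. A test that ignores the second factor puts its effect into the error variance. Vitamin D is expected to move 25(OH)D, so the outcome most exposed is 25(OH)D compared between HCS and usual care.

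That contrast is of some interest here: the Background suggests that HCS may ease barriers to taking supplements, and the third aim covers nutritional status. If it is reported from a one-factor t test, its confidence interval may be wider than the design requires. Because the two allocation lists are separate, the HCS and usual-care groups can also differ by chance in their share of supplemented women, and the t test does not remove that difference.

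**Working it through.** **Inputs from the article.** n = 300 v 300 per comparison; alpha 0.025 (two-sided assumed, since sidedness is not stated); difference 0.25 SD, or about 3 nmol/l for 25(OH)D. The implied SD is 3/0.25 = 12 nmol/l. The article does not say whether this is the SD within supplement group or pooled over supplement and placebo. It gives no expected vitamin D effect; 3 nmol/l is the difference to be detected.

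**The plan's own figure.** The standardised difference is 3/(12 × √(2/300)) = 3.06. Noncentral t power at two-sided 0.025 is 79.2% (79.4% by the normal approximation), so the stated 80% reproduces. The matching sample size is 305 per group against 300 stated.

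**Effect of leaving out the other factor.** If the omitted factor shifts the outcome by D and is split 1:1, the SD in the one-factor test is √(SD² + D²/4).

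*Paired primary tests (HCS on diet quality, vitamin D on 25(OH)D).* If the other factor's effect is 0.25 SD, the variance is multiplied by 1 + 0.25²/4 = 1.016. Power falls from 79.2% to 78.5%, a loss of 0.7 points.

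*HCS on 25(OH)D, difference 3 nmol/l, with 12 nmol/l taken as the within-arm SD.* Every D here is an assumption:

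| Vitamin D effect D (nmol/l) | SD in t test | Variance ratio | Power, t test | Power, both factors |
|---|---|---|---|---|
| 3 | 12.09 | 1.016 | 78.5% | about 79% |
| 5 | 12.26 | 1.043 | 77.3% | about 79% |
| 10 | 13.00 | 1.174 | 71.9% | about 79% |
| 20 | 15.62 | 1.694 | 54.2% | about 79% |

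*The same contrast with 12 nmol/l taken as the pooled SD.* The t test keeps about 79% whatever D is. The within-arm SD is then √(144 − D²/4), and the two-factor model gains: about 80% at D = 3, 81% at D = 5, 87% at D = 10 and over 99% at D = 20.

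**Validity.** With exactly equal cells, the simulated type I error of the HCS t test on 25(OH)D was 2.3% at D = 3, 1.6% at D = 10 and 0.2% at D = 20, against a nominal 2.5% (4,000 runs each). With two independent lists it was 2.6–2.8%, within simulation error of nominal (standard error √(0.025 × 0.975/4,000) = 0.25 points). Power with independent lists was 71–73% at D = 10 and 54% at D = 20, against about 79% with both factors, which agrees with the table.

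**Chance imbalance between lists.** With 752 women (4 × 188) and 376 on each margin, treating the lists as independent and ignoring blocking, a cell expected to hold 188 has SD 6.9 and a 95% range of 175 to 201.

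**The case against.** A reader might infer that the article promises 80% power for HCS on 25(OH)D and fails to deliver it. The documents do not support that.

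- **The contrast is not clearly primary.** The aims pair each intervention with one outcome. The alpha is set by "Our power calculation uses an alpha of 0.025 taking into account the two primary outcomes of maternal vitamin D and maternal diet quality": two tests at 0.025 sum to 0.05, whereas four would sum to 0.10. The word for 'relevant' arms in the analysis section would be redundant if every factor were tested on every outcome. The wording on each comparison and both outcomes is loose enough to cover HCS on 25(OH)D, but never states a power for it.
- **The larger losses are hypothetical.** At the only vitamin D difference the article gives, 3 nmol/l, the loss is 0.7 points. Larger losses need a larger assumed effect and a within-arm reading of the SD. The dose rationale under Ethical considerations (bringing women into the normal range) may suggest more than 3 nmol/l, but gives no figure.
- **Separate lists do not bias the test.** Unequal cell sizes are ordinary sampling variation that the t test's standard error already covers.
- **The adherence rationale is about interaction.** If HCS acts through taking the study capsules, it raises 25(OH)D only in women given active capsules. The exploratory interaction already addresses that, and an additive model would not isolate it.

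All four points stand. It can also be said that model terms are often left to an analysis plan, which is not shown here. This limits the point but does not remove it, because the article does not stay silent: it names a one-factor test and ties regression to baseline differences alone.

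**Conclusion.** The point holds as a free improvement in precision, not as an error in validity or a shortfall against a stated power. As written, no main-effect test contains the other randomised factor.

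On the two paired primary tests the cost is negligible, provided the other factor's effect is 0.25 SD or less. For any HCS contrast on 25(OH)D, the cost ranges from under 1 power point to about 25 points (79.2% − 54.2%) as the assumed vitamin D effect rises from 3 to 20 nmol/l, with 12 nmol/l as the within-arm SD. With 12 nmol/l as the pooled SD, the t test loses nothing against the planned figure but forgoes the gain that the two-factor model would bring.

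Separately, the article leaves unclear which factor is tested on which primary outcome, and that should be settled in the text.

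**What to change.** 1. In Statistical analyses, replace the one-factor t tests with one linear model per continuous outcome containing both randomised factors (HCS yes/no, vitamin D yes/no). Read each main effect and its confidence interval from that model. For binary outcomes, put both factors in the corresponding regression.
2. Keep the HCS by vitamin D interaction as the separate exploratory step already planned.
3. In Sample size and power calculation and in Statistical analyses, state which factor is tested on which primary outcome at alpha 0.025. If an HCS contrast on 25(OH)D will be reported, give its status. Say also whether the SD behind the 3 nmol/l is within supplement group or pooled.

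The cost is wording and one residual degree of freedom (597 instead of 598 with 600 women). No extra data are needed, and where the other factor has no effect the result is essentially that of the t test.

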### Early pregnancy

At around 14 weeks gestation women attend the research clinic at Princess Anne Hospital. The timing of this appointment can be later if they are not recruited by 14 weeks. During the appointment, an interviewer-led questionnaire is administered to gather information on parity, baseline demographic features, diet, smoking, alcohol intake, exercise, sunlight exposure, general health, medication, psychological health and wellbeing, self-efficacy and food involvement. Diet is assessed using a 20-item food frequency questionnaire (FFQ) which was developed from a larger FFQ [23]. Data from the FFQ are used to produce a standardised score (with mean 0 and standard deviation 1.0). This score has been named the ‘prudent diet score’. The 20-item FFQ gives closely comparable scores to the full FFQ and can be used in settings where administration of a longer FFQ is not feasible.

For women in the Healthy Conversation Skills intervention group, this appointment also presents an opportunity for the first Healthy Conversation with a trained research nurse. Women are asked about their lifestyle and health behaviours and what they would like to do to ensure they have healthy pregnancies and healthy babies, and to set some goals for achieving this. Details of the conversations and goals are recorded in a Case Report Form and revisited at future appointments.

Women’s height, weight, skinfold thickness (triceps, biceps, subscapular and suprailiac) and grip strength are measured. Venous blood samples are taken and stored with the aim of measuring biomarkers of quality of diet, including beta carotene and vitamin D. With participants’ consent, blood pellets are stored to allow future DNA analysis.

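### The primary t tests make no planned use of the early pregnancy diet score and vitamin D sample, and adjustment depends on whichever baseline differences turn up

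*Protocol article*

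**What the plan says.** The Statistical analyses section plans a complete case analysis using *t* "tests to compare the two primary outcomes between the relevant intervention arms". It continues: "Multiple linear regression will be used to adjust for any differences identified at baseline". Binary outcomes follow the same rule: "To adjust for imbalances at baseline, logistic regression will be used". The section names no covariate, does not define when a difference counts as identified, and does not say whether the *t* test or the regression is decisive if they disagree.

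Both primary outcomes, in the Primary outcomes section, are 34 week values: plasma 25(OH)D, and diet quality from a 20-item FFQ. The Early pregnancy section plans an earlier measurement of each at about 14 weeks. For diet: "Diet is assessed using a 20-item food frequency questionnaire (FFQ) which was developed from a larger FFQ". For vitamin D, blood is taken and stored in order to measure "biomarkers of quality of diet, including beta carotene and vitamin D".

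On size, the Sample size and power calculation section says: "Our power calculation uses an alpha of 0.025 taking into account the two primary outcomes". With 300 women on each side of each comparison, it claims that "there is 80 % power at an alpha of 0.025" to "detect a 0.25 standard deviation difference in both diet quality score and vitamin D".

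**The concern.** In a randomised trial, baseline differences arise by chance. What makes a covariate worth including is how well it predicts the outcome, not whether it happens to differ between the arms. The earlier value of the same measurement is usually the best predictor available. A rule that waits for an imbalance leaves that predictor out in most realisations of the trial, and can bring in weak covariates that differ by chance.

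The rule also leaves the primary estimate undefined. Two analyses of each primary outcome may exist, the content of the second is settled after seeing the data, and no order of precedence is given. At stake are the precision of both main results and how confidently a reader can tell which result was planned.

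**Working it through.** **Inputs from the protocol article (Sample size and power calculation):** n = 300 per side of each comparison, difference 0.25 SD, alpha 0.025 per outcome, power 80%. The article does not say whether the test is one-sided or two-sided.

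**Assumed, because the article gives no figure:** the correlation r between the early pregnancy and the 34 week value, taken as 0.3, 0.5 and 0.7; and, for the trigger, that a difference counts as identified when the baseline comparison has p<0.05.

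**Step 1: reproduce the stated power.** Power = Φ(δ√(n/2) − z), with z = 2.241 for two-sided 0.025.
- δ√(n/2) = 0.25 × √150 = 3.062.
- 3.062 − 2.241 = 0.821, so power is 79.4% (79.2% with the noncentral *t*).
- 80% power needs 305 per side, against the 300 planned.
- A one-sided test at 0.025 would give 86%.

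The stated figure is therefore a two-sided, unadjusted calculation that takes no credit for a baseline covariate.

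**Step 2: pre-specified baseline adjustment.** The residual SD becomes √(1 − r²), so
- power = Φ(3.062/√(1 − r²) − 2.241);
- detectable difference at 80% power = (2.241 + 0.842) × √(2/300) × √(1 − r²);
- equivalent unadjusted n = 300/(1 − r²).

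| r | Power at 0.25 SD | Detectable difference (SD) | Equivalent n per side |
|---|---|---|---|
| 0 | 79% | 0.252 | 300 |
| 0.3 | 83% | 0.240 | 330 |
| 0.5 | 90% | 0.218 | 400 |
| 0.7 | 98% | 0.180 | 588 |

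**Step 3: the imbalance trigger.** In large samples the unadjusted statistic is Z_T = r·Z_B + √(1 − r²)·Z_A, where Z_B is the standardised baseline difference and Z_A the adjusted statistic, independent of Z_B. The rule uses Z_A if |Z_B| > 1.96 and Z_T otherwise. Simulation of these statistics (2,000,000 draws per setting) gave:

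| r | Power, trigger | Type I error, trigger | Type I error, more favourable result reported |
|---|---|---|---|
| 0.3 | 80% | 0.024 | 0.033 |
| 0.5 | 81% | 0.021 | 0.038 |
| 0.7 | 81% | 0.016 | 0.043 |

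A separate simulation of individual data (20,000 runs per setting) put the power under the trigger at 80 to 82% and agreed on the error rates within simulation error.

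The trigger recovers almost none of the gain because, under a p<0.05 criterion, it acts in only about 5% of trials. It is conservative because the *t* test is kept only when the baseline is close to balance, where the unadjusted statistic varies less than its standard error implies.

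**Step 4: missing baseline values.** If women without a baseline value were dropped, a fraction f, the equivalent n would be 300(1 − f)/(1 − r²). The gain disappears when f = r²: 9% missing at r = 0.3, 25% at r = 0.5, 49% at r = 0.7. Handling of missing baseline values therefore matters most when the correlation is low.

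**The case against.** The strongest reply is that nothing is broken. The *t* test is valid under randomisation, it matches the basis of the sample size, and it reaches the planned power. It can fairly be read as the primary analysis, with regression as support. Covariate lists and precedence are often left to an analysis plan, which is not shown here. The gain depends on a correlation that the protocol does not give, and at r = 0.3 it is only about 4 points. For 25(OH)D, samples some 20 weeks apart will often fall in different seasons, which may lower r. All of this stands as a limit on size. It does not remove the point, because the protocol states an imbalance-driven rule rather than leaving the matter open, and an analysis plan that fixed covariates in advance would have to depart from it.

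Two practical objections also stand. The baseline assay for 25(OH)D is an aim for stored blood, and the Abstract mentions blood for 25(OH)D only at 19 and 34 weeks. And the early pregnancy visit is also where capsules are issued and the first Healthy Conversation takes place. Its questionnaire is interviewer-led, and staff are not blind to the Healthy Conversation Skills (HCS) allocation. The article does not give the order of events within the visit, so the diet baseline might be open to influence by allocation.

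A reader might infer that the rule breaks the 0.025 level. The documents do not support that: the trigger alone gives 0.016 to 0.024, and an excess appears only if the better of two results is reported, which the protocol neither permits nor rules out. A reader might also fault the *t* test for ignoring the other randomised factor. That is minor: with balanced allocation, an effect of 0.25 SD for that factor adds only 0.125² = 0.016, or 1.6%, to the variance.

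**Conclusion.** The point holds as one of efficiency and clarity. The planned test is valid and adequately powered on its own terms, so it would be wrong to conclude that the trial is underpowered or that its error rate is inflated by design. What the plan gives up is precision available from data it already intends to gather: about 83%, 90% or 98% power at r = 0.3, 0.5 or 0.7, against 79% for the *t* test and about 80 to 82% under the trigger.

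These figures assume 300 women analysed per margin with no loss for missing baseline values, a linear relation between the two measurements, two-sided alpha 0.025 and a p<0.05 trigger. The direction holds for any correlation that is not negligible; the size is not known from the document. The lack of a stated order between the *t* test and the adjusted result is a secondary weakness. It matters only if results are chosen after the fact, when type I error would be about 0.033 to 0.043.

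**What to change.** - Make the primary analysis one pre-specified linear model per outcome: the 34 week value regressed on both randomised factors (HCS and vitamin D) and the early pregnancy value of the same outcome. For 25(OH)D, add season of the 34 week sample.
- Delete adjustment for differences found at baseline, and the matching rule for binary outcomes. Keep the *t* test as a supporting analysis.
- Keep the HCS by vitamin D interaction as the separate exploratory analysis for the third aim. The main-effects model forces the combined effect to equal the sum of the two, so it cannot show synergy.
- State that the early pregnancy FFQ and blood sample precede the first Healthy Conversation and the first capsule, after checking that this is so in practice.
- Keep women with a missing baseline value in the model, for example by mean imputation of the covariate or a missing indicator.

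The cost is wording, plus assay of the stored early pregnancy samples for 25(OH)D, which the Early pregnancy section already intends. No change to recruitment or visits is needed.

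### Covariates are picked by observed baseline imbalance, so the 14 week diet score is adjusted for only by chance; the planned 80% power stands, but precision available at almost no cost is given up

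*Protocol article*

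**What the plan says.** Under Statistical analyses, the two primary outcomes are compared by t test on complete cases. The next sentence reads: "Multiple linear regression will be used to adjust for any differences identified at baseline". Secondary outcomes are to be handled similarly, and the section repeats the idea for binary outcomes. It names no covariate, gives no criterion for what counts as a difference, and does not rank the t test against the regression.

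Under Early pregnancy, at the visit at around 14 weeks, "Diet is assessed using a 20-item food frequency questionnaire (FFQ) which was developed from a larger FFQ". The data "produce a standardised score (with mean 0 and standard deviation 1.0"). Under Primary outcomes, the diet outcome at 34 weeks uses a 20-item questionnaire with the same citation. Blood is also taken at the early visit with the aim of measuring vitamin D, and self-efficacy is asked about.

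Under Sample size and power calculation, "there is 80 % power at an alpha of 0.025 to detect a 0.25 standard deviation difference", with 150 women per cell, "equivalent to 300 participants per arm in each comparison between HCS and routine care".

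**The concern.** Allocation to Healthy Conversation Skills (HCS) is random, in blocks of 4, with no stratification stated. Any baseline difference between the arms is therefore chance, and its size says nothing about whether the variable predicts the outcome. A covariate earns its place by predicting the outcome. An earlier reading of the same score is the obvious candidate for the diet outcome, and it is already collected, but the rule uses it only when it happens to be imbalanced.

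Two things are at stake. The first is precision: adjustment for a predictive baseline narrows the interval for the HCS effect whether or not the arms are balanced. The second is clarity: when a difference is found, there will be an unadjusted and an adjusted estimate of the same primary effect, with no stated order between them, and the choice of covariates will have been made after looking at the data.

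**Working it through.** **Inputs from the article.** 300 v 300 analysed; difference 0.25 SD; SD 1.0; alpha 0.025 per primary outcome. Sidedness is not stated; two-sided is taken because it reproduces the stated power.

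**Assumed inputs.** The correlation r between the 14 week and 34 week diet scores is not given, so 0.3 to 0.7 is shown. The trigger for a difference is not given either; p<0.05 on the baseline score is assumed.

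**1. The plan's own figure.** Power = Φ(0.25·√(300/2) − 2.241) = Φ(3.062 − 2.241) = Φ(0.821) = 79.4%. The stated 80% reproduces, and it belongs to the unadjusted t test.

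**2. Adjustment fixed in advance.** The residual SD becomes √(1 − r²), so power = Φ(3.062/√(1 − r²) − 2.241). For r = 0.5 this is Φ(3.062/0.866 − 2.241) = Φ(1.294) = 90.2%.

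**3. The imbalance rule.** This was simulated with large-sample normal statistics (2 million draws per case): use the adjusted result if the baseline difference has p<0.05, otherwise the t test.

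| r | t test power | Adjustment fixed in advance | Adjust only if imbalanced | Type I error of that rule |
|---|---|---|---|---|
| 0.3 | 79.4% | 83.4% | 79.9% | 0.0235 |
| 0.5 | 79.4% | 90.2% | 80.6% | 0.0207 |
| 0.6 | 79.4% | 94.4% | 81.1% | 0.0185 |
| 0.7 | 79.4% | 98.0% | 81.5% | 0.0159 |

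The rule recovers little because chance triggers it in only about 5% of trials. A check by hand for r = 0.5, from a second simulation of 400,000 runs: the trigger fires in 5.05% of trials; in those the t test has 67.0% power and the adjusted analysis 90.2%. So the rule gives 79.45% + 0.0505 × (90.2% − 67.0%) = 80.6%, as tabulated.

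**4. If either result may be claimed when the rule triggers.** Type I error is 0.025 to 0.026 across r = 0.3 to 0.7, against a nominal 0.025.

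**5. How often the missing ranking would matter.** In triggered trials at the design effect, the two results disagree on significance in 20% (r = 0.3), 32% (r = 0.5) and 43% (r = 0.7) of cases. Over all trials that is 1.0%, 1.6% and 2.1%. Under the null, the t test in triggered trials rejects in 5.4%, 11.1% and 21.3% instead of 2.5%. The ambiguity is therefore rare, but it bites exactly when the rule is invoked.

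**The case against.** The strongest defence is that the design and the named test match. The trial is powered for an unadjusted t test, that test is valid, and the 80% is reached. A reader might infer that the trial loses power or is underpowered. The article does not support this: power under the imbalance rule is no lower than planned, and what is described is a gain not taken. Its size rests on a correlation that the article does not give; at r = 0.3 it is only 4 points.

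A reader might also infer that the type I error is inflated. Values of 0.033 to 0.043 arise for r = 0.3 to 0.7 if the adjusted model is always run and the better result may be claimed. The quoted sentence does not say that; it adjusts only for differences that are found.

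A third tempting reading is that there are two rival primary results throughout. The t test is named first and may well be meant to lead, and a second result exists only when a difference is identified. The fair criticism is that the order is not written down.

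Finally, this is a condensed article, and an analysis plan not shown may name covariates. That would excuse silence. Here the sentence itself fixes selection by observed imbalance, so a later plan could do better only by overriding it. That part of the concern stands.

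**Conclusion.** The point holds as a badly fixed covariate rule, not as a validity failure. The planned 80% power is correct. The trial forgoes between about 4 points (r = 0.3) and 19 points (r = 0.7) of power on the diet outcome that data already collected could supply. Put another way, 80% power needs 305 women per group unadjusted but 277, 229 or 156 at r = 0.3, 0.5 or 0.7.

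These sizes depend on the assumed correlations, on two-sided testing, and, for the imbalance rule, on the assumed p<0.05 trigger. The direction does not: for any non-zero correlation, adjustment fixed in advance gains precision at this sample size. Under the assumed trigger the error rate is on the conservative side if adjustment replaces the t test, and about 0.026 at most if either result may be claimed, so error inflation is no ground for the change. The grounds are unused precision, a t test that misleads in the trials where imbalance does occur, and an unstated order between two results.

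The same reasoning applies to 25(OH) vitamin D, the other primary outcome, though no gain was computed for it.

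**What to change.** Replace the sentence on adjusting for identified differences with one primary analysis per primary outcome, fixed in advance and run whatever the baseline table shows:

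- **Diet:** linear regression of the 34 week prudent diet score on HCS allocation and the 14 week score.
- **Vitamin D:** linear regression of 34 week 25(OH) vitamin D on supplement allocation and the early-pregnancy value, where measured. This must be the early-visit sample, not the 19 week sample mentioned in the Abstract, because capsules are issued at the 14 week visit.
- **Self-efficacy (secondary):** the same form, with its baseline value.

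Keep the t tests as supporting results, say that the regressions decide, and remove covariate selection by observed imbalance, including in the sentence on binary outcomes.

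The cost is small but not nil. A simple rule is needed for missing baseline values, for example filling in the overall mean without regard to arm. The questionnaire and the first Healthy Conversation share one appointment and their order is not stated, so the plan should confirm that the diet and self-efficacy questions are completed before the conversation; a score taken afterwards could already reflect the intervention. The trial is described as ongoing, so for visits already held this can only be checked. The change is most credible if made before outcomes are seen by arm. The diet and self-efficacy analyses need no new data; the vitamin D model needs the stored early sample to be assayed.
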